### **Statistical Analysis:**

For the observational phase, exploratory analyses will be undertaken to determine how well scores on the electrographic outcomes (evoked potentials, H-reflex testing, computerized posturography, surface electromyography) correlate with clinical outcomes such as gait disability, gait speed, and AIS motor and sensory scores. Using post hoc regression analysis, we hope to generate a preliminary model to predict anatomical and functional integrity of specific neural tracts based on performance on this battery of tests. This analysis and any resulting predictive model would need further validation with a prospectively studied population. The interventional phase of the study would not depend on the success of obtaining such a predictive model.

For the interventional phase of the study, participants will be randomly assigned to receive either locomotor training followed by multimodal training, or multimodal training followed by locomotor training. The primary outcomes will be change in tibialis anterior motor-evoked potential amplitude and change in lower extremity motor score (LEMS) compared to baseline. All other outcomes are secondary and exploratory.

The most rigorous method of analyzing data from crossover studies involves the use of independent-sample rather than paired-sample tests (Wellek & Blettner 2012). Therefore, outcome measures will be calculated within each subject as the percent change between baseline and completion of each intervention. The percent change across all subjects for each training modality will be compared using independent-sample t-tests or Mann-Whitney U tests depending on the normality of the data distribution. To test for the possibility that the washout period does not fully eliminate carryover effects, the percent change across all subjects for each training period (pre-washout, post-washout) will also be compared using independent sample tests. Statistical significance for all outcomes will be corrected for multiple comparisons using Bonferroni's method.

**Power Calculation:** Given that our training protocol is novel, we need to make predictions by extrapolating from other types of protocols. This is further hampered by the fact that most SCI

rehabilitation studies involve rather small numbers of participants in often inadequately controlled studies.

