The most applicable study upon which to base our power analysis measured MEP amplitudes before and after 60-100 sessions of treadmill training in eight subjects with incomplete thoracic SCI (Thomas & Gorassini 2005). They found a  $46 \pm 12\%$  increase in maximal MEP amplitude post-training. Additionally, studies in uninjured volunteers demonstrated a 40-70% increase in MEP amplitudes with skilled training exercises but not passive movement or strength training (Jensen et al. 2005; Perez et al. 2004).

Due to these and other factors, we project an improvement of 50% with MULTIMODAL training versus 25% with TREADMILL training. The use of a crossover design will reduce inter-subject variability between the two training modalities compared to a parallel-group design. We conservatively project an estimated variance of 25% for each group – this magnitude of variance is larger than the average variance seen in the MEP studies cited above. Based on these numbers, the calculated power to detect a difference between the two training groups on a two-tailed independent-sample *t*-test or Mann-Whitney test is greater than 80% with 18 subjects, at an  $\alpha = 0.05$ . We will enroll 24 subjects to account for up to a 25% dropout rate.

|                | Year 1 | Year 2 | Year 3 | Total N |
|----------------|--------|--------|--------|---------|
| Phase 1 | 15     | 18     | 18     | 51      |
| Phase 2 | 6      | 10     | 8      | 24      |

**Table 3** Clinical Study Timeline – Participants enrolled per year.

**3a. Basic Information** (Even if described under “Procedures”, list the information requested below where pertinent.)

The study will occur in two phases: An observational phase, in which participants will undergo a series of clinical and neurophysiological tests; and an interventional phase, in which participants with incomplete SCI will undergo standard LOCOMOTOR training and experimental MULTIMODAL training in random order. Training will continue for 48 sessions per intervention, separated by a 6-week washout period. The clinical and neurophysiological tests will be repeated at the end of each intervention.

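### Single-step Bonferroni is valid but gives up power: Holm on the two primary outcomes gives the same error control and never less power, with a gain that depends on a LEMS effect the protocol does not state

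*Protocol*

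**What the plan says.** The Statistical Analysis section of the protocol names two primaries for the interventional phase: "The primary outcomes will be change in tibialis anterior motor-evoked potential amplitude and change in lower extremity motor score (LEMS) compared to baseline". It then sets the rest apart: "All other outcomes are secondary and exploratory". The multiplicity rule, however, covers everything: "Statistical significance for all outcomes will be corrected for multiple comparisons using Bonferroni". The section mentions no step-down procedure and does not say how many comparisons form the family.

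The power calculation covers MEP amplitude only. Its inputs are "we project an improvement of 50% with MULTIMODAL training versus 25% with TREADMILL training" and "We conservatively project an estimated variance of 25% for each group", with a test "on a two-tailed independent-sample" in form and alpha 0.05. The stated result is power "greater than 80% with 18 subjects", followed by "We will enroll 24 subjects to account for up to a 25% dropout rate". No effect, standard deviation or power is given for LEMS, and no correlation between the two primaries.

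**The concern.** The protocol fixes the multiplicity method itself, so this is not a detail left to a later document. With two hypotheses, single-step Bonferroni compares both p-values with 0.025. Holm does the same for the smaller p-value but, once that is significant, compares the larger with 0.05. Nothing is lost by the change:

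- If both nulls are true, an error requires the smaller p-value to be at or below 0.025. This has probability at most 0.025 + 0.025 = 0.05 under any dependence.
- If only one null is true, an error requires that p-value to be at or below 0.05.

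The plan counts on 18 completers and only modestly exceeds 80% power for MEP before any correction. LEMS is the clinical primary beside an electrophysiological one, so a result on both would be the more persuasive finding. That joint result is where single-step Bonferroni costs most.

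**Working it through.** **Inputs from the protocol.** MEP difference 50 − 25 = 25 points. The 25% variance is read as a standard deviation of 25 points, so d = 25/25 = 1.0. There are 18 values per modality, since each participant receives both trainings. The test is two-sided and treats the samples as independent, as the power statement does.

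**Inputs assumed.** LEMS standardised effect from 0.25 to 1.0; correlation between the primaries from 0 to 0.8; a confirmatory family of two.

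**Reproducing the plan's figure.** Noncentral t, d = 1.0, n = 18 per modality, two-sided 0.05: power 0.830, which agrees with the stated figure above 80%. Reading 18 as 9 per group gives only 0.513, so 18 per modality is the reading that fits. Enrolment also reproduces: 18/(1 − 0.25) = 24.

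**Bonferroni with two tests.** The same calculation at 0.025 gives 0.741.

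**Holm, closed form at correlation 0, LEMS d = 1.0.**
- One primary: 0.741 + (0.830 − 0.741) × 0.741 = 0.807, a gain of 6.6 points.
- Both primaries: Bonferroni 0.741² = 0.549; Holm 0.830² − (0.830 − 0.741)² = 0.681, a gain of 13.2 points.

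**Weaker LEMS, correlation 0.** Holm's MEP power is 0.741 + 0.089 × (LEMS power at 0.025).
- LEMS d = 0.75: 0.741 + 0.089 × 0.471 = 0.783
- LEMS d = 0.5: 0.741 + 0.089 × 0.213 = 0.760
- LEMS d = 0.25: 0.741 + 0.089 × 0.067 = 0.747

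**Simulation with correlation** (bivariate normal data, 100,000 trials per setting). Gains are in percentage points and were taken before rounding.

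| LEMS d | Correlation | MEP gain | LEMS gain | Both: Bonferroni to Holm | Gain |
|---|---|---|---|---|---|
| 1.0 | 0 | 6.6 | 6.6 | 0.549 to 0.681 | 13.2 |
| 1.0 | 0.5 | 5.3 | 5.5 | 0.610 to 0.718 | 10.9 |
| 1.0 | 0.8 | 4.7 | 4.6 | 0.652 to 0.746 | 9.3 |
| 0.75 | 0 | 4.2 | 8.8 | 0.350 to 0.480 | 13.0 |
| 0.75 | 0.5 | 2.7 | 9.0 | 0.410 to 0.527 | 11.7 |
| 0.75 | 0.8 | 1.1 | 10.0 | 0.453 to 0.564 | 11.1 |
| 0.5 | 0 | 1.9 | 7.0 | 0.158 to 0.247 | 8.9 |
| 0.5 | 0.5 | 0.8 | 8.3 | 0.196 to 0.286 | 9.1 |
| 0.5 | 0.8 | 0.1 | 9.2 | 0.210 to 0.303 | 9.3 |
| 0.25 | 0 | 0.6 | 3.5 | 0.050 to 0.090 | 4.0 |
| 0.25 | 0.5 | 0.2 | 4.2 | 0.062 to 0.106 | 4.3 |
| 0.25 | 0.8 | 0.0 | 4.4 | 0.064 to 0.108 | 4.4 |

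At correlation 0.6 and LEMS d = 1.0, MEP power goes from 74.1% to 79.1% and power for both from 62.1% to 72.3%.

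**Checks.**
- The chance of at least one significant primary is the same under both methods (0.934 at correlation 0, LEMS d = 1.0).
- Family-wise error with both nulls true is identical (0.049 at correlation 0; 0.047 at 0.5).
- With MEP d = 1.0 and LEMS null, the false-positive rate for LEMS rises from 0.025 to 0.043, still below 0.05.
- If all 24 complete with d = 1.0 on both, the gains are 3.1 to 4.7 points per primary and 6.3 to 9.3 for both.

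**If all outcomes form one family.** Two primaries plus the 14 numbered items under Secondary outcomes make at least 16 tests, since some items hold more than one measure. At 0.05/16, with independent outcomes, Bonferroni power per primary is about 0.44. Holm across all 16 then adds:
- 0.4 points per primary and 0.8 for both, if the secondary outcomes are null;
- 1.3 and 1.7, if they have d = 0.5;
- about 11 and 12, if every outcome has d = 1.0.

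**The case against.** The strongest reply is that nothing here is wrong. Bonferroni is valid and common, and the protocol makes no false statement in choosing it. That stands, so the point concerns efficiency only. It remains worth raising because the alternative needs no extra assumption and no extra data.

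Three stronger readings are tempting, and the protocol does not support them.

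- A reader might infer a fixed gain of 5 to 7 points per primary and 10 to 13 for both. Those figures need a LEMS effect as large as the MEP effect, and the protocol gives none. With a weaker LEMS effect the MEP gain nearly vanishes, although the LEMS and joint gains remain material down to d = 0.5.
- A reader might infer that the protocol tests the two primaries as a family of two at 0.025. Its sentence corrects all outcomes and states no divisor. Read literally it could mean 16 or more tests, where Holm across the whole set would add little. The two-test family is the natural reading of the split between primary and exploratory outcomes, but it has to be written down.
- A reader might infer that the trial needs both primaries to succeed, or that Holm raises its chance of any success. The protocol sets no both-must-win rule, and the chance of at least one significant primary does not change.

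It is also fair to say that the larger problem in this section is power computed at 0.05 while testing is corrected: 0.83 falls to 0.74 with two tests and to about 0.44 with 16. Holm makes up only part of the two-test loss, and only if LEMS also responds.

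**Conclusion.** The point holds as a free improvement. For the two primaries, Holm dominates single-step Bonferroni: the same family-wise error bound and never fewer rejections. That statement needs no assumption.

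Its size does. It rests on a family of two, 18 values per modality, MEP d = 1.0 (the 25% variance read as a standard deviation), independent-sample testing and correlation 0 to 0.6. Within that:

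- LEMS d = 1.0: about 5 to 7 points per primary, 10 to 13 for both.
- LEMS d = 0.75: about 2 to 4 for MEP, 9 for LEMS, 12 to 13 for both.
- LEMS d = 0.5: about 1 to 2 for MEP, 7 to 8 for LEMS, 9 for both.
- LEMS d = 0.25: under 1 for MEP, about 4 for LEMS and for both.

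The benefit therefore falls mainly on LEMS and on the joint result, and much less surely on MEP, the only outcome the protocol powers.

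**What to change.** In the Statistical Analysis section, replace the all-outcomes Bonferroni sentence with wording to this effect: the confirmatory family consists of the two primary outcomes, tested by Holm's procedure at family-wise 0.05; the smaller p-value is compared with 0.025 and, if significant, the larger with 0.05; secondary and exploratory outcomes lie outside this family, and any correction among them does not change its divisor.

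Naming the family is an essential part of the change, since Holm over 16 or more outcomes would add only about 1 point per primary unless most of them have large effects.

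The cost is a sentence or two of wording, settled before results are seen, with no change to participants, data or procedures. The power statement should be corrected separately so that its alpha matches the testing rule.

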**Clinical Tests**

- Physical Examination – A standard physical and neurological exam will be performed. This will include seated and upright blood pressure testing.
- American Spinal Injury Association (ASIA) Impairment Scale – Manual assessment of muscle strength in the arms and legs, as well as assessment for sensation in the arms, trunk, legs, and perineal area.
- Modified Ashworth Scale – Leg muscle spasticity will be qualitatively assessed during the clinical exam on a scale of 0 to 4.
- Spinal Cord Assessment Tool for Spasticity (SCATS) – Three components of spasticity in the lower extremity – clonus, extensor spasm, and plantar response – will be timed in response to standardized evocative maneuvers (Benz et al. 2005).

- Berg Balance Scale – Balance and postural stability will be qualitatively assessed in seated, lying, and standing positions. Most patients will not be able to perform the standing portions of the scale. See **Table 1** for details of seated balance section.
- 10-meter walk test (10MWT) – Ambulatory participants will be asked to walk 10 meters at their best pace. The time to cover this distance will be timed with a stopwatch. Assistive devices will be used if necessary – participants using an assistive device at baseline will be retested with the same assistive device at follow-up visits after training.
- Walking Index for Spinal Cord Injury II – Participants will be graded on a scale of 0-20 based on the degree of assistive device support required for walking 10 meters (Ditunno Jr. et al. 2007).
- Seated 10-second step test – Participants with the ability to move their legs will be seated with their hips and knees flexed to 90 degrees. Steps will consist of lifting one foot entirely off the ground and placing it back down again. The average number of steps taken during three 10-second trials with each foot will be recorded.
- Grasp-and-release test – Participants with cervical-level injury in seated position will be asked to grasp a standardized bottle, pick it up, move it approximately 25 cm, then place it down and release. The average number of successful grasp-and-releases taken during three 30-second trials with each hand will be recorded.
- Pinch dynamometry – In participants with cervical-level injury, pinch strength will be recorded using a wireless dynamometer (JTech Freedom Tracker). The average of three maximal pinch strengths in each hand will be recorded.
- McGill Pain Questionnaire (short form) – Chronic neuropathic pain commonly plagues subjects with SCI. This short (less than 5 minutes), validated survey will provide a baseline to track whether any neural plastic changes result in adverse effects on neuropathic pain.
- Spinal Cord Injury Spasticity Evaluation Tool (SCI-SET) - This survey evaluates how spasticity impacts a person's activities of daily living over the course of the previous 7 days. The survey uses a bidirectional Likert scale to detect both negative and positive impacts of spasticity (Adams et al. 2007).
- SCIQoL - Participants will complete a questionnaire regarding physical/medical health, emotional health, physical function, and social participation. A research assistant will conduct the interview. The questionnaire is located on an online platform called Assessment Center. The Assessment Center database is housed at Northwestern University and analyzed by a team at the University of Michigan. No HIPAA identifiers will be collected through the online platform.
- WHOQOL-BREF Questionnaire – This tool assesses general quality of life, and has been internationally validated for use in the SCI population. It is briefer than the computer-adapted SCI-QOL survey and will be used specifically to correlate with findings on the SCI-SET and SCATS (World Health Organization 1998).

### **Radiographic/Physiological Tests**

- Dual Energy X-ray Absorptiometry (DXA). A whole-body DXA scan will be obtained using a Lunar iDXA (GE) located in our COE on 7A-13. Data will include bone densitometry for the spine, femurs, and knees. There is no discomfort associated with this test. Participants will be asked to lie on a semi-padded, fixed table-top for about 30-40 minutes while being scanned. If the participant's scan is set to the highest setting (e.g., thicker regional mass will require a higher setting for the scanning mode), the following will be the delivered radiation exposure:

| Site       | Irradiation time (sec) | Estimated skin entrance dose ( $\mu\text{Gy}$ ) | Effective Dose ( $\mu\text{Sv}$ ) |
|------------|------------------------|-------------------------------------------------|-----------------------------------|
| Total Body | 739                    | 6                                               | 8.62                              |
| Dual Femur | 212                    | 329                                             | 12.3                              |
| AP Spine   | 104                    | 329                                             | 6.8                               |

|      |    |    |         |
|------|----|----|---------|
| Knee | 54 | 34 | No Data |
|------|----|----|---------|

**Table 4** – Radiation exposure during dual energy X-ray absorptiometry. Note: Values of effective dose (absorption) for the knee in  $\mu\text{Sv}$  do not exist at this time, but considering the intensity and the duration of the scan is less than or equal to that of the other scans, the absorbed amount will also be lower (GE Medical systems, Madison WI).

- Motor evoked potentials (MEP) – This technique will be performed using a MagPro R30 system (MagVenture) located in the COE on 7A-13 (FDA 510K approval #K061645). Muscle responses to TMS and the other procedures described below will be recorded using a Viking Select EMG system (Natus) or a Trigno wireless EMG system (Delsys). Inducing MEPs with transcranial magnetic stimulation is a standard technique used to assess the CST's ability to propagate signals to muscles above or below spinal lesions, through direct and/or detour pathways (McKay et al., 2005). A stimulator coil will be positioned appropriately over the motor cortex to evoke action potentials while recording from key muscle groups: first dorsal interosseous (C8); tibialis anterior (L4); and soleus (S1). Recruitment curves at escalating stimulation intensities will be determined, including the percent output required to reach peak MEP amplitude ( $\text{MEP}_{\text{max}}$ ) and the threshold required to produce a detectable MEP ( $\text{MEP}_{\text{thresh}}$ ), all as described (Thomas and Gorassini, 2005). Note that this use of TMS does *not* involve *repetitive* TMS. Repetitive TMS is a separate entity utilized to achieve modulation of brain activity. Even though it is considered to be higher-risk than diagnostic/single pulse TMS, repetitive TMS has been FDA-approved for treatment of refractory major depression. This repetitive TMS device (NeuroStar) is in clinical use at the JJPVAMC Department of Psychiatry (FDA 510K approval #K083538).
- Soleus H-reflex facilitation – All electrical stimuli will be performed using the Viking Select system or a Grass S88 dual-output stimulator (Natus) or a DS7A stimulator (Digitimer). This test provides insight on descending supraspinal influence over a spinal reflex located below the injury level. Electrical pulses (1ms duration) will be applied via surface electrodes in the popliteal fossa (over the tibial nerve) to stimulate the H-reflex, as recorded by electrodes over the soleus muscle. A range of pulse intensities will be delivered to determine the threshold and maximum amplitude of the H-reflex ( $H_{\text{max}}$ ), slope of the H-reflex recruitment curve, and maximal direct soleus response amplitude (maximal M-wave or  $M_{\text{max}}$ ). To test TMS-facilitated H-reflex response, TMS intensity will be set at 90% of resting motor threshold (ie, subthreshold stimulus) (or 80% of maximum stimulator output if no active motor evoked potentials are obtainable from the TA). H-reflex stimulation intensity will be set to elicit an H-reflex of 10-20% of  $M_{\text{max}}$  (Serranova et al. 2008). A series of paired pulses will be delivered every 10 seconds in intervals of 0-120ms apart (TMS before H-stimulus). The paired-pulse time intervals and unconditioned H-stimuli will be varied at random. At each time interval, the amplitude of the TMS-conditioned H-reflex (averaged over 3-5 stimuli) will be compared with the non-conditioned H-reflex amplitude to determine the magnitude of facilitation. For example, if non-conditioned H-reflex amplitude is 0.5mV, whereas H-stimulus preceded 60ms earlier by subthreshold TMS results in a reflex of amplitude 0.9mV, the magnitude of facilitation would be 180% at that time point. This procedure is already IRB-approved (SPU-12-07).
- Soleus H-reflex pre-synaptic inhibition (PSI) – This test measures the magnitude of peroneal nerve-mediated PSI of tibial nerve Ia afferent fibers. The spinal interneurons involved in this circuit are influenced by descending supraspinal connections (Iles 1996). Peroneal nerve stimulation (at 95% of tibialis anterior motor threshold) will be delivered as 3x1 ms pulses at 333 Hz, 21 ms prior to tibial nerve stimulation (Roche et al. 2011). The amplitude of the conditioned H-reflex (averaged over 3-5 stimuli) will be compared with the non-conditioned H-reflex amplitude to determine the magnitude of inhibition.
- Soleus  $H_{\text{max}}/M_{\text{max}}$  – This measure serves as an electrophysiological proxy for lower limb spasticity (Trimble et al. 2001). It will be derived from the standard procedure of stimulating the tibial nerve over a range of intensities. H-reflex amplitudes will be fitted to a sigmoid

function(Klimstra & Zehr 2008). Tibial nerve stimulation intensity will be increased until  $M_{max}$  is obtained. Higher ratios of  $H_{max}$  to  $M_{max}$  correlate with increased spasticity.

- Soleus H-reflex reciprocal inhibition – Reciprocal inhibition is essential for reducing interference between agonist and antagonist muscles(Knikou & Mummidisetty 2011). This circuit is similar to the PSI circuit described above – peroneal nerve stimulation leads to interneuron-mediated inhibition of soleus alpha motor neurons. As with PSI, the interneurons mediating reciprocal inhibition are influenced by descending brainstem and corticospinal pathways(Knikou & Mummidisetty 2011; Morita et al. 2001). Peroneal nerve stimulation (at 95% tibialis anterior motor threshold) will be delivered at varying intervals prior to tibial nerve stimulation to find the interval and magnitude of maximal inhibition (usually less than 5 ms)(Roche et al. 2011). The amplitude of the conditioned H-reflex (averaged over 3-5 stimuli) will be compared with the non-conditioned H-reflex amplitude to determine the magnitude of inhibition.
- Computerized Posturography – Posturography testing will be performed using the Smart Equitest device located in ENT clinic (2C-07). The Smart Equitest device (Neurocom; FDA 510K approval #K851744) has been in clinical use by the Audiology Clinic for the past four years to test patients with balance and vestibular disorders. The device consists of floor pressure plates embedded in a computerized movable platform. Software-controlled protocols test the effects of different types of balance perturbations on the participant's ability to maintain and adjust the center of gravity. Importantly, posturography testing can be performed in either a standing or sitting position. Response times and muscle activity of the legs (either volitional or reflexive) will be recorded. We will focus on the Limits of Stability (LOS) testing paradigm. In the LOS test, participants are asked to shift their center of gravity toward eight different surrounding targets. Key measures are endpoint excursion of the center of gravity, and the directional accuracy of intended movements – the sensors and software calculate each of these measures automatically.
- Brain Motor Control Assessment (BMCA) – Multichannel EMG assessments will be performed using surface (not needle) electrodes connected to a Viking Select system (Natus) or a Trigno wireless system (Delsys) located in 7A-13. Changes in leg muscle activity will be monitored during relaxation, reinforcement maneuvers (e.g. flexing neck against resistance), and voluntary movements. Key muscle EMG amplitudes and time-to-peak values will be determined. In this way, several measures of motor control and neural responsiveness will be analyzed, providing insight into the presence of residual cortical and brainstem circuitry running through spinal lesions.

